In the retrospective study of 294 patients with primary supratentorial HGGs undergoing elective tumor resection, anesthesia maintenance with sevoflurane did not significantly worsen the PFS of the patients compared with propofol. However, sevoflurane might decrease the OS in patients with a Karnofsky Performance Status (KPS) scale of less than 80 [12]. The KPS scale is subjectively evaluated and recorded by a neurosurgeon preoperatively based on the following hierarchical scale: 100=normal, no evidence of disease; 90=able to perform normal activity with only minor symptoms; 80=normal activity with effort, some symptoms; 70=able to care for self but unable to do normal activities; 60=requires occasional assistance, care for most needs; 50=requires considerable assistance; 40=disabled, require special assistance; 30=severely disabled; 20=very sick, requires active supportive treatment; and 10=moribund.

The OS of patients with lower KPS were more influenced by the choice of anesthetics. Several reasons might be related to the results. Firstly, sevoflurane increases cerebral blood flow and decreases the cerebral metabolic rate by decoupling of the relationship between blood flow and oxygen consumption of the brain tissue. It increases ICP and reduces the compliance of brain tissue, which aggravates the neurofunction of the lower KPS patients [13]. However, propofol reduces cerebral blood flow and cerebral oxygen consumption simultaneously, which benefits for brain tumor patients with higher ICP. Secondly, compared with sevoflurane, propofol reduces the release of inflammatory factors and vascular permeability, which may reduce the severity of encephaloedema, and contribute to the complete resection of the tumor and the early recovery of patients [14]. Lastly, propofol improves postoperative analgesia and promotes rapid recovery compared with inhalational anesthetics [15, 16]. So propofol has been recommended for better ICP control and cerebral hemodynamics of patients in neurosurgical anesthesia [17, 18]. In the retrospective study, the lower KPS patients mainly included the aged, weak, disabled, or paralyzed patients. The anesthesia methods might affect the long-term outcome through aggravating the neurofunction and systematic condition of patients, however, their effects on tumor malignancy, invasiveness, and host cellular immunity have not been identified.

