### Randomization and blinding

Block randomization will be conducted via computer-generated codes by an independent research assistant who will pack the allocation sequence with identical sequentially numbered opaque envelopes and distribute to the researcher according to the enrolling sequence. The independent research assistant should not recruit and allocate the participants for the purpose of avoiding selection bias.

Patients will be randomly assigned to the two groups at a 1:1 ratio. At the surgery morning, just before anesthesia induction, the trained attending anesthesiologists will receive the sealed envelope and know about the grouping. They will perform anesthesia strictly following the protocol and record intraoperative information. Trained follow-up personnel will not participate in the clinical anesthesia and postoperative management, or know the records of other researchers. The researcher assistant, patients, and outcome assessors will be blinded to the allocation, intraoperative management, or perioperative information until the completion of the study analysis unless specific circumstances, such as the occurrence of a serious adverse event (SAE).

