### Data collection and management

After obtaining informed consent, an independent research assistant will initiate baseline information collection one day before surgery. All personal information will be kept strictly confidential for research purposes only. Basic demographic information, including gender, age, vital signs, body mass index, past medical history, family history, smoking and drinking history, allergy history, operation history or anesthesia history, medication history, age-adjusted Charlson comorbidity index (aCCI, a widely used scoring system to predict outcomes of variety of medical conditions and malignancies, including the age of the patient as a correction variable of the final score of the CCI with the addition of one point for every decade over 40 years), ASA classification, KPS, Glasgow coma scale (GCS) will be collected. Functional classification of tumor (indicating the resectability of tumor) will be evaluated according to the results of preoperative MRI (Supplementary Table 4) [31, 32].

Intraoperative viable include vital sign parameters during anesthesia, total dose or infusion rate of anesthetic agents or other drugs during operation, such as inotropic or vasoactive drugs, mannitol, estimated blood loss, urine volume, the type, and dose of fluid and blood transfusion, duration of surgery and anesthesia. The usage of the analgesia pump (dosage, number of compressions, and effective compressions) will be recorded.

Postoperative medication will be recorded including sedative, analgesia, glucocorticoids, mannitol, and fluid infusion on 1 to 3 days postoperatively. The extent of resection (EOR) will be evaluated by a professional neuro-radiologist according to the results of the MRI within 72 h postoperatively (Supplementary Table 4).

The median follow-up time will be 18 months postoperatively before the study was terminated. The patients and their legal representatives will be told to be followed up by telephone at 3, 6, 9, 12, 15, and 18 months postoperatively. The start points of simultaneous radiotherapy and chemotherapy, patient compliance, adverse events or complications and treatment, the European organization for the research and treatment of cancer on quality of life (EORTCQLQ-C30), and the Karnofsky performance Status (KPS) Scale will be evaluated every 3 months postoperatively. Strict data management will be kept including double data entry and establishing range checks for data values.

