### Sample size calculation and statistical analysis

The sample size is estimated by using PASS 2011 software (NCCS LLC). We calculated the sample size based on the primary outcome. A two-sided Log-rank test with an overall sample size of 344 subjects (172 in the intravenous group and 172 in the inhalation group) achieves 80% power at a 0.05 significance level to detect a hazard ratio of 1.66 when the overall survival is 15 vs. 11 months in intravenous and inhalation group, respectively. The study will last for about 42 months, of which subject accrual (entry) occurs in the first 24 months with the proportion dropping out of the two groups being 0.1, respectively.

Analysis will be conducted using SPSS software (version 23.0). The Kolmogorov-Smirnov test will be used to test data normality. Normally distributed continuous variables will be described as the means with standard deviation (SD) and compared by using independent *t* tests. Non-normally distributed variables will be summarized as medians and interquartile range (IQR) and compared by using Mann-Whitney *U* tests. Categorical variables will be described as numbers (*n*) and percentage (%) and compared using chi-square or Fisher’s exact tests.

The Kaplan-Meier method will be used to describe the time-to-event data (OS and PFS), and the log-rank test will be used for comparisons. Univariate and multivariate Cox proportional hazard regressions will be used for survival analysis. Together with the anesthesia type, variables with *P*<0.1 in the univariate analysis will be regarded as candidate variables for the multivariable model. A significance level of *P*<0.05 will be used to indicate statistical significance. The imputation method will be used for dealing with missing data. The impact of missing data will be estimated by sensitivity analysis. Additionally, subgroup analysis will be undertaken to assess the association between anesthesia and the outcome according to the aCCI, KPS, EOR, WHO grade, duration of anesthesia, and whether using chemotherapy or not. No interim analysis will be done and the trial will not early terminate.

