## Discussion

This is a randomized controlled trial to compare the effect of intravenous or inhalation anesthesia maintenance on the OS in supratentorial HGG patients of KPS<80. There are some well-known risk factors such as age at diagnosis, KPS, histological type, distant metastasis, and extent of surgical resection for predicting the OS of patients with HG G [31].

Intravenous and inhalation anesthesias are the common anesthesia methods for HGG resection. But they are different in some aspects. Firstly, intravenous anesthesia inhibits the invasion of the tumor cells and host stress response and protects cellular immunity, while inhalation anesthesia has the opposite effect. Secondly, during craniotomy, the mass effect of the tumor and the peritumoral edema always lead to severe intracranial hypertension and brain herniation. As nearly all inhalational agents increase the cerebral blood flow and ICP, propofol has the opposite effect to decrease the ICP and facilitate tumor exposure. Thirdly, intravenous anesthesia promotes postoperative rapid recovery of the patients. Postoperative pain, nausea and vomiting, and shivering appear less frequently with propofol-maintained anesthesia [16, 33, 34]. However, the hemodynamic stability, time to extubation, and early cognitive functions were similar with two anesthetic techniques [35].

In this RCT study, we will fully evaluate the patients before operation, including physical status, neurological function, and imaging results. During the operation, standard anesthesia management, anesthesia depth monitoring, and individualized medication according to the protocol will be conducted by specially trained personnel. After surgery, the patients will be followed up regularly by designated personnel for the recovery, adverse events, complications, treatment, PFS, and OS.

Although the intervention of our study is intravenous or inhalation anesthesia, inhalational anesthetics will not be used for induction, as it is not routine in clinical practice. So propofol induction will be used in both groups. We regard the effect of a single bolus of propofol as minimal and short, which will be eliminated completely before surgical incision.

We use the survival time to calculate the sample size. As the median OS was 15 vs.11 months in TIVA and inhalation group, with a hazard ratio of 1.66, the calculated sample size is 344, which is more credible in survival analysis.

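### Three of the six planned subgroup factors (extent of resection, anaesthesia duration, chemotherapy use) are settled after randomisation, so treatment effects within them are not protected by randomisation and can be biased

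*Protocol article*

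**What the plan says.** The section on sample size and statistical analysis plans to examine the anaesthetic effect in subgroups formed "according to the aCCI, KPS, EOR, WHO grade, duration of anesthesia, and whether using chemotherapy or not". It attaches no caveat to any of the six factors.

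The article also fixes when each factor becomes known:

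- **Allocation:** "At the surgery morning, just before anesthesia induction, the trained attending anesthesiologists will receive the sealed envelope and know about the grouping" (Randomization and blinding).
- **Extent of resection:** graded "according to the results of the MRI within 72 h postoperatively" (Data collection and management).
- **Anaesthesia duration:** "duration of surgery and anesthesia" is listed among the intraoperative variables (same section).
- **Chemotherapy:** its start is recorded at the three-monthly postoperative contacts (same section).
- **Overall survival:** counted from the day of surgery (Outcomes).

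On whether the anaesthetic can move these factors, the Background describes effects of propofol "which may reduce the severity of encephaloedema, and contribute to the complete resection of the tumor and the early recovery of patients", and the Discussion says that "propofol has the opposite effect to decrease the ICP and facilitate tumor exposure". The Discussion also lists extent of resection among the known predictors of survival, and reports similar times to extubation with the two techniques.

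**The concern.** Randomisation makes the arms comparable within any subgroup defined by what was already true at allocation. It gives no such assurance for a subgroup defined by something that happens later and may depend on the arm. Two problems can follow.

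- **Removing part of the effect.** If propofol prolongs survival partly through more complete resection, comparing the arms within resection strata takes that part out. It answers a different question from the trial's.
- **Selection.** If the arm alters who enters a stratum, the patients compared within it differ in prognosis. That can produce an effect, or a difference between strata, that does not exist.

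At stake is the reading of three secondary tables. A misleading one would matter in this trial, whose population of patients with KPS below 80 was itself chosen after a subgroup signal in a retrospective study.

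**Working it through.** **1. Timing of the six factors.**

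| Factor | When settled | Before allocation? |
|---|---|---|
| aCCI, KPS | baseline, the day before surgery | yes |
| WHO grade | read after surgery, but a property of the tumour already present | yes, in substance |
| Extent of resection | MRI within 72 h after surgery | no |
| Anaesthesia duration | during surgery | no |
| Chemotherapy use | postoperative follow-up | no |

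Three of six are post-randomisation. The protocol states no figure to reproduce, so the sizes below are illustrations. Inputs that it does not give are marked as assumed.

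**2. Extent of resection: loss of a mediated effect.** Assumed: exponential survival, median 13 months with complete resection, follow-up cut at 18 months; hazard 1.5 or 2 times as high with incomplete resection; complete resection 10 or 20 percentage points more frequent with propofol; no other effect of the anaesthetic. Cox HR, propofol versus sevoflurane:

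| Gain in complete resection | Hazard multiple if incomplete | Total HR | HR within either stratum |
|---|---|---|---|
| 10 points | 1.5 | 0.96 | 1.00 |
| 10 points | 2 | 0.94 | 1.00 |
| 20 points | 1.5 | 0.93 | 1.00 |
| 20 points | 2 | 0.87 | 1.00 |

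Stratum values are 1.00 by construction; simulated ones lay between 0.99 and 1.01. Varying the sevoflurane complete-resection rate from 40% to 60% changed the total HR by less than 0.01. A real benefit of treatment disappears from both strata.

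**3. Extent of resection: selection.** Now let an unmeasured prognostic factor influence both resectability and survival (assumed: standard normal, log-hazard coefficient 0.3 or 0.6; complete resection lowers the log hazard by 0.4; no direct anaesthetic effect). HR, sevoflurane versus propofol:

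- no difference in resection: strata 0.99 to 1.02;
- 10-point difference: strata 0.93 to 0.97, overall 1.03 to 1.05;
- 20-point difference: strata 0.89 to 0.95, overall 1.08.

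Where resection differs, the strata point the opposite way to the overall result.

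**4. Chemotherapy: who can be a user.** A patient who dies before chemotherapy starts is a non-user. With the protocol's medians of 15 and 11 months and exponential survival, the share dead by month t is 1 − 2^(−t/median):

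- t = 1.5 (assumed start): 1 − 2^(−0.100) = 6.7% versus 1 − 2^(−0.136) = 9.0%;
- t = 3 (assumed start): 1 − 2^(−0.200) = 12.9% versus 1 − 2^(−0.273) = 17.2%.

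Membership of the strata therefore depends on the arm whenever early survival differs.

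**5. Chemotherapy: size when the effect is early.** Assumed: gamma frailty with mean 1 and variance 0.5; hazard 0.04 per month for two months, multiplied by 1.5 or 2 with sevoflurane; equal hazards afterwards (ln 2/12 per month); chemotherapy in 80% of those alive at 1.5 months; it modifies nothing. Uptake is 0.8 × (1 + 0.5 × hazard × 1.5)^(−2):

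- propofol: 0.8 × 1.030^(−2) = 75.4%;
- sevoflurane, 1.5-fold: 0.8 × 1.045^(−2) = 73.3%;
- sevoflurane, 2-fold: 0.8 × 1.060^(−2) = 71.2%.

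Simulated HR, sevoflurane versus propofol:

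| Early hazard | Overall | Users | Non-users |
|---|---|---|---|
| 1.5-fold | 1.05 | 1.00 | 1.16 |
| 2-fold | 1.10 | 1.00 | 1.30 to 1.31 |

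**6. Chemotherapy: size when the effect is constant.** With HR 1.66 throughout, 80% uptake and a 3-month start, the simulated HRs were 1.64 overall, 1.63 in users and 1.54 in non-users (1.55, 1.52 and 1.48 with prognostic heterogeneity). With no survival difference there was no distortion beyond simulation noise.

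**The case against.** **The distortion is conditional.** A reader might infer that these subgroup effects are biased as a matter of fact. The documents do not support that. Bias needs the arm to change the factor or early survival, and steps 3 and 6 show little or none when it does not. This stands.

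**Resection does not show a false interaction.** Step 2 gives 1.00 in both strata: a masked mediated effect, not a difference between subgroups. This also stands, and that case is argued here only as masking.

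**Immortal time is the wrong label.** That bias distorts users against non-users. Here the arms are compared within a stratum, and users in both arms had to survive to the start. The mechanism is selection on a post-randomisation variable, and it needs an early survival difference between arms.

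**The chemotherapy scenario is favourable to the concern.** It puts the whole effect in the first two months, and uptake and start time are assumed. At 344 patients the non-user stratum would hold about 88 to 92 patients and 58 to 62 deaths. The chance of P<0.05 there would be about 9% to 18%, and about 7% to 13% for an interaction test, against a nominal 5%. The inflation is modest even so.

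**Duration is thinly supported.** Its dependence on the arm is inferred from the remarks on intracranial pressure and exposure, and the reported similar extubation times point the other way.

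**These are additional analyses, and an analysis plan may exist.** No decision is tied to them, and interaction tests or landmark methods may be set out in a plan not shown. Their absence is not the finding. The finding is the choice of the three factors, which the article does state.

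**Conclusion.** The point holds in this form: three of the six named factors are post-randomisation, and treatment effects within them are not protected by randomisation and can be biased.

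Support differs by factor. It is strongest for extent of resection, because the protocol's own rationale places it on the path from anaesthetic to survival. It is sound but conditional for chemotherapy: the distortion ranges from none to HR 1.00 versus 1.31, depending on whether the arms differ in early survival. It is weakest for duration, where only the timing is certain.

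The count and timing rest on the text. Every HR above rests on assumed inputs and shows a possible size, not an expected one. The log-rank comparison of overall survival and the sample size are untouched. The change is worth making because it is nearly free and prevents three tables from being read as randomised evidence.

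**What to change.** In the statistical analysis section:

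- Limit treatment-effect subgroups to aCCI, KPS, WHO grade and the preoperative functional classification of the tumour. The last grades resectability on preoperative MRI, is already collected, and can replace extent of resection.
- Assess each by a treatment-by-subgroup interaction.
- Report extent of resection, anaesthesia duration and chemotherapy use descriptively by arm.
- Label any analysis of the anaesthetic effect by these three as exploratory and non-randomised, with a landmark or time-dependent approach for chemotherapy.

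The cost is wording. Three planned subgroup tables are dropped or relabelled. No new data are needed, and sample size, conduct and the primary analysis do not change.

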### Reporting of adverse events

Data monitoring committee will not be set up in the trial for the sample size is not very large. However, an auditing trial will be conducted twice per year and the process will be independent from investigators and the sponsor. All adverse events (AEs) will be closely monitored until a stable situation has been reached. The chief investigator will be informed of any serious AEs and determine the severity and causality of these events. All AEs associated with this study will be recorded and reported to the Ethics Committee as part of the annual report. The chief investigator will be responsible for collecting the details about the causes of AEs, treatment, prognosis, and reporting SAE to the Ethics Committee immediately. The incidence of adverse effects will be described as percentages and frequencies for each group. Chi-square and Fisher’s exact test will be used for comparison between groups. The researcher will have access to the final trial data set.

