### Protocol amendment

The chief investigator will be responsible for any decision to amend the protocol. If there is any modification (e.g., changes to eligibility criteria, outcomes, or analysis), the principle investigator will report and gain approval from the China Ethics Committee of Registering Clinical Trials prior to implementation, by communicating with relevant other members (e.g., investigators, participants, registries, journals, and regulators).

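### Early termination is ruled out with no safety exception, which is hard to reconcile with immediate SAE reporting, and no one is named to review deaths and SAEs by arm

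*Protocol article*

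**What the plan says.** Protocol article, *Sample size calculation and statistical analysis*: "No interim analysis will be done and the trial will not early terminate". No safety exception is attached here or in any other section.

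Protocol article, *Reporting of adverse events*:
- "Data monitoring committee will not be set up in the trial for the sample size is not very large". This is the only reason given.
- "an auditing trial will be conducted twice per year and the process will be independent from investigators and the sponsor". What the audit examines is not described.
- "The chief investigator will be informed of any serious AEs and determine the severity and causality of these events".
- The chief investigator is also responsible for "reporting SAE to the Ethics Committee immediately", and "All AEs associated with this study will be recorded and reported to the Ethics Committee as part of the annual report".
- Adverse effects are to be compared between groups, with no time stated for that comparison.

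Two other provisions bear on the point. *Randomization and blinding* keeps the blind "unless specific circumstances, such as the occurrence of a serious adverse event (SAE"). *Protocol amendment* says "The chief investigator will be responsible for any decision to amend the protocol" and requires ethics approval before a change takes effect.

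The primary outcome is overall survival within 18 months, in patients with a preoperative KPS below 80 (*Outcomes*; *Study population*).

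**The concern.** Doing without an efficacy interim analysis is a legitimate choice. Excluding a stop for harm is a separate decision and does not follow from it. The sentence makes both decisions at once, and the second sits badly with immediate SAE reporting, whose purpose is to let an outside body act.

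No section gives anyone the task of looking at deaths or SAEs by arm while patients are still being randomised. The chief investigator judges each serious event singly. In high-grade glioma with poor performance status, death is common and a single death will seldom look related to the anaesthetic. An excess in one arm would normally show only when the arms are set side by side.

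The stated reason for having no committee does not address this. For monitoring, what counts is the number and nature of the events, and here the main event is death.

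At stake is the protection of patients not yet randomised. There is also a practical risk: an Ethics Committee that wished to halt recruitment would meet a protocol sentence saying that this will not happen.

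**Working it through.** **1. The provisions side by side.**

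| Provision | Section | Handles single events? | Stated to compare arms during accrual? |
|---|---|---|---|
| Chief investigator judges each serious AE | Reporting of adverse events | Yes | No |
| SAEs to the Ethics Committee at once | Reporting of adverse events | Yes | No |
| AEs in the annual report | Reporting of adverse events | Yes | Not stated |
| Half-yearly independent audit | Reporting of adverse events | Content not described | Not stated |
| Unblinding for an SAE | Randomization and blinding | Yes | No |
| Amendment with ethics approval | Protocol amendment | Not applicable | No |
| No interim analysis, no early termination | Sample size calculation and statistical analysis | Not applicable | Rules out an interim analysis |

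Each route deals with individual events or with procedure. None is described as a comparison of arms, and the last row, read literally, closes off the strongest action that the others could lead to.

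**2. Expected deaths on the plan's own assumptions.** Inputs from *Sample size calculation and statistical analysis*: 172 per arm, survival of 15 and 11 months (called medians in the Discussion), accrual over 24 months. The plan gives no death count to reproduce. Assumptions added here: exponential survival, uniform accrual, 18 months of follow-up per patient, no dropout.

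Monthly hazards: λ = ln 2/15 = 0.04621 and ln 2/11 = 0.06301. Accrual per arm: 172/24 = 7.167 per month.

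For t up to 18 months, deaths per arm = 7.167 × [t − (1 − e^(−λt))/λ].

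- Month 12, 15-month arm: 7.167 × [12 − (1 − 0.5743)/0.04621] = 7.167 × 2.789 = 20.0
- Month 12, 11-month arm: 7.167 × [12 − (1 − 0.4695)/0.06301] = 7.167 × 3.581 = 25.7
- Month 18, 15-month arm: 7.167 × [18 − (1 − 0.4353)/0.04621] = 7.167 × 5.779 = 41.4
- Month 18, 11-month arm: 7.167 × [18 − (1 − 0.3217)/0.06301] = 7.167 × 7.235 = 51.9

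At month 24, the first 6 months of entrants have completed 18 months, which adds 6 × (1 − e^(−18λ)) inside the bracket: 7.167 × (3.388 + 5.779) = 65.7 and 7.167 × (4.070 + 7.235) = 81.0.

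In total: 172 × (0.5647 + 0.6783) = 213.8.

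| Month | Randomised | Still to be randomised | Expected deaths |
|---|---|---|---|
| 12 | 172 | 172 | 46 |
| 18 | 258 | 86 | 93 |
| 24 | 344 | 0 | 147 |
| 42 | 344 | 0 | 214 |

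About 86 patients (344/4) are randomised between one half-yearly audit and the next.

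**3. What a strict bound on cumulative deaths could detect.** With z = ln(HR) × √(D/4) and the death counts above:

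| Month | z at HR 15/11 = 1.364 | z at the stated HR 1.66 | HR at which z = 3.29 |
|---|---|---|---|
| 12 | 1.05 | 1.71 | 2.65 |
| 18 | 1.50 | 2.45 | 1.98 |
| 24 | 1.88 | 3.07 | 1.72 |

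The planned effect would not, on average, cross 3.29 during accrual. Such a bound reacts only to a much larger difference.

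**4. Cost in type I error.** One look at half the information at |z| > 3.29, with the final test left at 1.96, gives a total two-sided alpha of 0.0502 and power of about 80%. For looks at months 6, 12, 18 and 24, with information fractions 0.06, 0.21, 0.44 and 0.69 from step 2 (12.6 deaths at month 6), simulation of the joint normal statistics gives a total alpha of about 0.052. The chance of crossing at any of the four looks when the arms are equal is about 0.4%.

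**The case against.** **No one could act on harm.** A reader might infer this, and the documents do not support it. SAEs reach the chief investigator and, at once, the Ethics Committee; the blind may be broken for an SAE; an audit is independent of investigators and sponsor; and the protocol can be changed with ethics approval.

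**The reporting routes could never lead to a stop.** This too goes further than the text. The sentence stands in the statistical section, joined to the statement on interim analysis, and may mean only that no statistical look will end the trial. Nothing says that the Ethics Committee gives up its authority. What stands is that the wording is absolute and that the two sections must be reconciled.

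**A condensed article may leave monitoring detail to the full protocol.** That is fair for the content of the audit, which might include a look by arm. It does not cover an explicit rule and an explicit reason that are both in print.

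**The death counts are not a measure of harm.** Correct. They are mostly deaths expected from glioma, and both arms use routine techniques. The counts show only that event numbers are not small. Extending the exponential curve back to the day of surgery would say nothing reliable about perioperative mortality, for which the documents give no figure.

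**Exposure ends with surgery, and the planned effect would not cross a strict bound before accrual ends.** Also correct (step 3). Review by arm therefore protects only patients not yet randomised, chiefly against a large excess, whether in cumulative deaths or in early deaths and SAEs.

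**A table of deaths by arm is a look at the primary outcome.** Correct. With two active arms and a two-sided test, excess deaths in one arm are superiority of the other. The amendment must say so.

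**Conclusion.** The point holds in limited form. The protocol article excludes early termination without a safety exception, and this is hard to reconcile with its own immediate SAE reporting and half-yearly independent audit. It names no one to review accumulating deaths or SAEs by arm. Its only reason for having no committee, sample size, is weak when the primary outcome is death.

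On the planning medians, about 46 deaths are expected when half the patients are still to be randomised, and about 93 when a quarter are. These figures rest on exponential survival, uniform accrual and no dropout. They describe the volume of events and are no evidence that either arm is unsafe. The omission of an efficacy interim analysis is not criticised. The change should be made because it concerns patient safety and costs little.

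**What to change.** 1. Replace the sentence in *Sample size calculation and statistical analysis* with: *There will be no interim efficacy analysis, and the trial will not stop early for benefit or futility. Recruitment may be suspended or stopped for safety by the Ethics Committee.*
2. In *Reporting of adverse events*, have the existing half-yearly independent audit send the Ethics Committee a closed table of early postoperative deaths, cumulative deaths and SAEs by coded arm. Investigators and outcome assessors do not see it.
3. Delete the sample-size reason for having no monitoring committee.
4. State that the table is a look at primary-outcome data, that a safety stop will not be reported as an efficacy result, and that a stop on cumulative deaths needs strong evidence fixed in advance, for example a Haybittle-Peto type bound.

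Cost: one amendment with ethics approval and one closed table twice a year. With a bound of |z| > 3.29, total alpha stays between 0.050 (one look) and 0.052 (four looks), and the chance of crossing it on cumulative deaths through random imbalance alone is about 0.4% over four looks. The sample size need not change.
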